### Study instruments

The primary outcome of the study is the rate of BMI growth. We hypothesize that in the intervention arm, the rate of BMI growth will be less than the comparison community after three years of the intervention. We assess BMI, abdominal circumference and skinfold thickness in eligible children in both communities every six months. Anthropometric measurements are conducted in accordance with methods defined in the Anthropometric Standardization Reference Manual [16] and by a medical team consisting of trained staff and student surveyors from UCD, and trained local staff. Staff training consists of at least one, 3-hour anthropometric training and an observation session in which the trainees team up with experienced surveyors to gain hands-on experience. A digital scale by Seca (model 874) is used to weigh participants to the nearest 0.1 kg. A stadiometer (Seca 213) is used to measure height in centimeters (cm) to the nearest 0.1 cm. Abdominal circumference is obtained by using a QuickMedical QM2000 body circumference measuring tape. Finally, skinfold thickness of the triceps and subscapular regions are measured using Lange calipers (Beta Technology, Santa Cruz, CA).

Training and standardization manuals are developed and used in order to ensure precision and standardization of data. All the surveyors involved in measurement are standardized in order to assure accuracy and validity of measurements. The technical error of measurement (TEM) is used to calculate inter-observer and intra-observer errors [17]. For the inter-observer error, the surveyors compare their results to the lead anthropometrist. Standardization occurs before each anthropometric data collection period.

All measurements are conducted in duplicate. If the two measurements differ more than a certain pre-defined level, a third measurement is taken. At least two surveyors are involved in conducting anthropometric measurements. Steps are taken in order to protect the participants’ privacy and to minimize discomfort. In group settings, such as at the community center or at health fairs, anthropometric measurements are conducted in tents and participants are provided with disposable hospital gowns, and data are entered directly in the computer database. When measurements are conducted in participants’ homes, data are recorded on paper and are entered into a computer after leaving the home.

In order to fully understand underlying factors that may impact behavioral choice in these families, five surveys are administered at baseline and within defined intervals throughout the study (Table 2). Each participating family is required to complete baseline surveys as well as the anthropometric measurements to start the intervention. The surveys include: (1) United States Department of Agriculture Household Food Security tool (USDA-FS 2); (2) the Food Frequency Questionnaire (FFQ); (3) the Household Baseline Survey; (4) the Brief Acculturation Rating Scale for Mexican Americans (ARSMA); and (5) the Physical Activity Reporting Form (PARF).

**Table 2 T2:** Variables, measures and instruments

**Survey measure**	**Data level**	**Instrument**		**Measured construct**	**Time Interval**	**Setting**
Anthropometric measurements	Individual	Weight	Digital scale	Anthropometric measures	6 months	School, health fair, NSFS office, participants’ homes
		Height	Stadiometer			
		Abdominal circumference	Body circumference measuring tape			
		Triceps skinfold thickness	Calipers			
		Subscapular skinfold thickness	Calipers			
Medical history	Individual Family	Medical History Survey		Family and personal medical history	1 year	Health fair, NSFS office, participants’ homes, phone-interview
Food security	Family	USDA Household Food Security Tool (FS)		Food Security	6 months	Health fair, NSFS office, participants’ homes
						Phone-interview
Nutrition	Individual	Food Frequency Questionnaire (FFQ)		Child eating patterns and feeding practices	6 months	Health fair, NSFS office, participants’ homes
						Phone-interview
Acculturation	Family	Brief Acculturation Rating Scale for Mexican Americans (ARSMA)		Acculturation	Baseline	Health fair, NSFS office, participants’ homes
						Phone-interview
Physical activity	Individual	Polar Accelerometer		Physical activity	1 year	School, health fair, NSFS office, participants’ homes
	Class	Class Physical Education Reporting Form		Physical activity	Weekly	Elementary and pre-school sites
Household baseline survey	Household	NHANES		Food purchasing patterns	1 year	Health fair, NSFS office, participants’ homes
		CPS		Demographic Information		
		NLSY		Income		
		ECLS-K		Expenditure		
		Local level WIC		Assets		

The USDA-FS includes 18 items. Food security is defined as 0–2 affirmative responses; low food security as 3–7 affirmative responses; and very low food security as 8 or more affirmative responses to the questionnaire [18]. This tool is used to monitor food security in the U.S. and is validated for use in a Mexican-origin population in California [19-21]. In these validation studies, food insecurity is correlated with lower household supplies of fruits and vegetables [22], which, in turn, is associated with lower intakes of these foods in preschool children [23]. Administration of the tool occurs using in-person and telephone interviews by trained students and staff surveyors. The in-person interviews are conducted at large gatherings, the field office and home-visits. Stations are set up with screens to provide privacy and assure confidentiality for all the participants.

We capture child eating patterns and feeding practices with the Food Frequency Questionnaire (FFQ) constructed of 30 questions and accompanied pictures. The tool includes 26 items related to the frequency of consuming specific foods over the past 30 days measured on a Likert scale. We selected 26 items based on studies previously validated in a binational study of Mexican-origin families [24]. In that study, an Americanized food pattern including frequent consumption of hot dogs, hamburgers, fried chicken, pizza, instant soup, instant cereal, and American cheese was significantly correlated with BMI-z-score in Mexican-origin preschoolers (r = +0.21, P < 0.0008) and demonstrated good internal reliability (Cronbach’s alpha =0.70). Four items are included in this scale to examine the structure of meals and snacks and parental role modeling at mealtimes, adapted from the Hughes Caregiver scale [25]. The development of this pictorial version of the FFQ includes a pilot testing with seven *promotores* from the intervention community. Only one FFQ is collected from each family regardless of the number of eligible children. Where more than one child is eligible, the parent is asked to respond for either a child between 4 and 5 years of age and who is not in kindergarten. If a child does not fall within these age categories, the response is based on the child closest in age to that window.

We use the Household Survey (HHS), which is designed and conducted to obtain information on food purchasing patterns, demographic information, income, expenditure, assets, and neighborhood characteristics of participating families. The household survey is based on previously tested and administered questionnaires from national and local levels [26-30]. Team members reviewed the surveys, compiled and edited questions that are relevant to the NSFS research objectives and study population. The survey was translated to Spanish and all questions were piloted with the intervention and comparison communities in order to ensure level of understanding of the questionnaire and elimination of questions as needed. An HHS manual was created to train surveyors. Surveyors completed a training course to learn about surveying techniques, data integrity, and the household survey instrument. After the initial training, new surveyors observe a survey being conducted by an experienced surveyor before conducting a survey. An experienced member also observes new surveyors during their initial interviews. Household surveys are collected by in-person interviews. Surveyors administer the surveys using netbooks and capture data electronically. The average time to administer the survey is 45 minutes for a seasoned surveyor, but varies depending on family size and situation. Surveyors complete a survey log to indicate surveyor, duration of the survey, language used to complete the survey and any annotation or information that might need to be clarified during the cleaning stage of the data.

Participating families in both communities answer the Brief Acculturation Rating Scale for Mexican Americans (ARSMA) [31]. The ARSMA consists of two subscales, an Anglo Orientation Subscale and a Mexican Orientation subscale. Within this population the ARSMA scale is used extensively with good internal reliability and strong construct validity and is only administered at baseline [31].

To track school-based physical education, pre-school and K-2^nd^ grade teachers in the intervention group are asked to record their daily delivery of formal (i.e. teacher-led, structured) physical activity (excluding recess) using a weekly form developed and tested by the researcher and teachers. K-2^nd^ grade teachers in the comparison district are asked to not change their regular physical activity levels and to record formal classroom physical activity sessions (excluding recess) on the same reporting form as the treatment teachers. Both groups are asked to identify each day of the week and minutes each day that children are engaged in formal or in-class physical activities. For each physical activity session, teachers record the specific activity performed by the students and the level of exercise noted as Low, Medium, or High. These data are turned into their supervisors and collected by program staff.

In addition to the survey tools, we use other methods of data collection. In order to measure actual household food purchase/consumption data, we collect retail store purchasing data. Scanners are installed in the Firebaugh Supermarket and families are given a loyalty card to use at the store during every transaction. Data for every item purchased is automatically recorded through the scanning software. These scanner data will be collected during the intervention and follow-up years from participants in the intervention community of Firebaugh and automatically sent and stored in a central server. In addition, families are instructed to collect and turn in food receipts from stores other than Firebaugh Supermarket. In the comparison group, all food receipts will be collected during the monthly nutrition workshops. These data will be transferred to a central database and linked to the household data set.

Physical activity is assessed in a subset of eligible children enrolled in the study once per year using a PolarActive™ unidirectional accelerometer (Figure 2). This device provides continuous 24-hour measurement of total energy expenditure (kcal), number of steps, sleep duration, and time spent in each of five intensity zones (very easy, easy, moderate, vigorous, and vigorous+). The development and validation of this device have previously been described [32]. Briefly, physical activity measurement with this device has shown good correlation (R = 0.93) with oxygen consumption measurement in children [32].

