A major goal of *Niños Sanos, Familia Sana* is to reduce the rate of growth of childhood obesity among Mexican-origin children between the ages of three and eight by improving the economic capacity of low-income, Mexican-origin families, enhancing the nutritional skills of families, supporting the capacity of schools to more effectively provide Physical Education (PE) opportunities for children in preschool and K-2 settings, and providing community art programs that allow for nutrition and positive behavioral health messaging. Biannual anthropometric data, annual physical activity data and annual household survey data are collected of our sample population, which allow us to determine the impact of behavioral and community intervention factors on rate of growth of childhood obesity within our study population. These data are compared to our comparison community that receives a non-nutrition community-based intervention.

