### Statistical analysis

#### Sample size calculation

During the baseline phase of the study, all eligible children and their families in both Firebaugh and San Joaquin are approached. Based on an initial estimation of the total number of children from previous years, we anticipated that our sample would contain approximately 400 children in each group. This number of subjects is sufficient to detect an effect difference between groups in the mean change in standardized BMI (z-scores) of as small as 0.20 standard deviations with 80% power. In a previous study with Latino school children, a change of that magnitude was achieved over a two-year period.

Our sample constructs a multi-cluster formation of students, classrooms, grades, schools and cities. Because we are not assigning multiple cities to each group, we have to assume that the matching of cities will take care of any clustering problem at the city level. However, accounting for clustering is a problem in sample size calculation because there is really no way of estimating in advance the within-cluster correlation (r) with respect to any of the outcome variables. To our knowledge this information is not available from other studies. If we assume that r = 0.01 among school grades in schools and there are an average of 143 students per grade then based on the design effect formula (DE = 1 + (n-1)*r), the detectable effect difference in primary outcome will be 1.56 * 0.20 standard deviation with 80% power in this study. Based on the school’s estimation there will be less than a 5% mobilization rate within the targeted schools. All new students who fall in our sampled cohort will be eligible for the study.

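### The declared primary outcome is the rate of BMI growth over three years, but the sample size and power are given for mean change in BMI z-score

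*Protocol article*

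**What the plan says.** The Study instruments section defines the endpoint: "The primary outcome of the study is the rate of BMI growth". The hypothesis is that, in the intervention arm, "the rate of BMI growth will be less than the comparison community after three years of the intervention". The data come from repeated visits: "We assess BMI, abdominal circumference and skinfold thickness in eligible children in both communities every six months". No z-score, percentile or reference population is attached to the outcome there. The Abstract and the research goals in the Background also speak of the rate of BMI growth without standardisation.

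The Sample size calculation section uses another quantity. It expects that "our sample would contain approximately 400 children in each group" and says this suffices to detect "an effect difference between groups in the mean change in standardized BMI (z-scores) of as small as 0.20 standard deviations with 80% power". The effect size is supported by an earlier study of Latino school children in which "a change of that magnitude was achieved over a two-year period". The section then allows for clustering by school grade, multiplies 0.20 SD by 1.56, and reports the result as the effect detectable in the primary outcome.

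**The concern.** Two quantities carry the label of primary outcome. One is a rate of change in BMI judged at three years. The other is a mean change in BMI z-score with a two-year precedent. A result on one need not agree with a result on the other, and the article does not say which decides the trial. If both stay open, the choice of scale can follow the results. The power statement, the only quantitative support for the study's size, belongs to just one of them.

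The scale matters in this age range. Expected BMI change in young children varies with age and sex, which is why standardised scores exist; the article does not say this, and I take it as general knowledge. The design has one town per arm, and new students who fit the cohort may join. If the towns' enrolled children differ in age mix, an unadjusted comparison of raw BMI growth would carry part of that difference, whereas a z-score would largely remove it.

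**Working it through.** **1. Reproduce the stated sizing.** Inputs from Sample size calculation: about 400 per group, difference 0.20 SD, power 80%. The significance level is not stated; I assume 0.05 two-sided.

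- Needed per group: 2 × (1.960 + 0.842)² / 0.20² = 393, against about 400 planned.
- Power at 400 per group for 0.20 SD: 80.7%.
- Detectable difference at 400 per group: (1.960 + 0.842) × √(2/400) = 0.198 SD.
- A one-sided 0.05 test would need 310 per group and give 88% power at 400, so it does not fit the stated figures.

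**2. Reproduce the clustering factor.** Inputs: r = 0.01 and 143 students per grade.

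- Design effect: 1 + 142 × 0.01 = 2.42.
- Factor on the detectable effect: √2.42 = 1.556, which the article rounds to 1.56.
- Detectable effect: 1.56 × 0.20 = 0.312 SD.

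Both steps agree with the article.

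**3. Set the two definitions side by side.**

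| | Study instruments | Sample size calculation |
|---|---|---|
| Scale | BMI, no standardisation mentioned | BMI z-score |
| Form | rate of growth | mean change |
| Horizon | three years | two-year precedent |
| Label | primary outcome | primary outcome |

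**4. Try to carry the power over to a BMI slope.** The formula would be n per group = 2 × (1.960 + 0.842)² × (SD of slope)² / (target slope difference)², times the design effect. The article gives neither an SD of the BMI slope nor a target in kg/m² per year. The power for the outcome as declared therefore cannot be computed.

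**5. Check what 0.20 is measured in.** The calculation reproduces if 0.20 means SDs of the change. If it means z-score units, the answer depends on the SD of the change. Assume a z-score SD of 1 at each time and correlation ρ between the two times, so that the SD of change is √(2(1 − ρ)). All values of ρ are assumptions, and clustering is left out.

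| ρ | SD of change | 0.20 SD of change, in z units | Power if 0.20 is z units, 400 per group |
|---|---|---|---|
| 0.5 | 1.000 | 0.200 | 80.7% |
| 0.7 | 0.775 | 0.155 | 95.5% |
| 0.8 | 0.632 | 0.126 | 99.4% |
| 0.9 | 0.447 | 0.089 | >99.9% |

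The two readings coincide only at ρ = 0.5, so the unit needs to be stated.

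**The case against.** The best defence is that the authors meant z-scores throughout. The outcome definition names no scale, the word raw appears nowhere, and the sample size section itself calls the z-score effect the primary outcome. This stands in part: raw BMI is the plain reading, since the article writes z-score elsewhere when it means one, but it is not the document's word. If z-scores were intended, the Study instruments section states the outcome incompletely and still needs correction, and a rate judged at three years still differs from a mean change with a two-year precedent.

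It can also be said that an article need not give the analysis model, and that age and sex adjustment may be in a plan not shown. That is fair, and I do not treat the missing model as a fault. Adjustment could deal with age mix, but it would not make a z-score power statement apply to BMI growth.

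Three stronger readings are tempting and are not supported.

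- *That the Background sets a third endpoint.* It describes an aim "to reduce the rate of growth of childhood obesity among Mexican-origin children between the ages of three and eight". This is a statement of goals; it defines no outcome variable.
- *That the towns' age mix is likely to be unequal.* Both share one birth window and grade rule (Table 1), all children in a grade are recruited, and all eligible children in both towns are approached. Unequal uptake is possible but not shown.
- *That age mix alone could produce nearly the whole 0.20 SD target.* This needs assumed inputs. Take BMI slopes of −0.2 kg/m² per year at ages 3–4 and +0.4 at 7–8, a 10-point difference in age mix, and an SD of three-year change of 1 to 2 kg/m². Then 0.10 × 0.6 × 3 = 0.18 kg/m², or 0.09 to 0.18 SD. But this freezes each child's slope for three years. With linear interpolation, 0.6 over four years of age is 0.15 per year of age. A child followed from 3 to 6 and one followed from 5 to 8 have mid-ages of 4.5 and 6.5, so their slopes differ by 0.30. That gives 0.10 × 0.30 × 3 = 0.09 kg/m², or 0.045 to 0.09 SD. The benchmark after clustering is 0.312 SD, so the two versions amount to 29–58% and 14–29% of it. None of the slopes, SDs or mix differences is in the article.

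**Conclusion.** The point holds as an inconsistency within the article. The primary outcome as defined and the quantity that was powered differ in scale, form and horizon. The sizing arithmetic is correct for a z-score change, given an assumed two-sided 5% level. The stated 80% power, for 0.20 SD or 0.312 SD with clustering, cannot be claimed for the rate of BMI growth as declared, and the power for that outcome cannot be computed from what is given.

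Bias from age mix in an unstandardised comparison is a real possibility with one town per arm and an open cohort. It is a reason to prefer the standardised scale. Neither its presence nor its size can be established from the article, so no figure for it belongs in the conclusion.

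**What to change.** Name one primary variable and one time point, in the same words, in Study instruments and Sample size calculation. The natural choice is the between-town difference in change, or slope, of age- and sex-standardised BMI z-score from baseline to three years, because it matches the powered quantity and is far less sensitive to age mix. Make unstandardised BMI secondary, adjusted for age and sex. Change versus slope is a matter of choice; what matters is that one is fixed before outcomes are compared between the towns. Bring the goal wording in the Abstract and Background into line.

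State whether 0.20 is in z-score units or in SDs of the change, and restate the detectable effect for the named outcome at three years, with clustering. If the outcome is change in z-score and 0.20 means SDs of that change, the existing 0.20 and 0.312 SD carry over. If it is a slope, or if 0.20 means z-score units, an SD for the slope or the change must be supplied, and the article gives none.

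The cost is small: a reworded outcome, a restated power sentence and a little analysis work. Height and weight are already scheduled every six months, so no new measurement is needed.

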**Figure 2 F2:**
[figure not shown]
Polar™ Active accelerometer.

The accelerometer protocol was developed to target participants aged 5–7 y. Each eligible child uses the device which is worn on the wrist for seven consecutive days, allowing for the collection of five complete days of data inclusive of at least one weekend day. Children and their parents are verbally instructed to not remove the accelerometer during the period of use, including during water-based activities (e.g., bathing, swimming) and while sleeping. Parents are provided a diary to note any removals, including the time, duration and reason for removal. As part of the protocol development, a qualitative pilot was conducted with children in a rural community similar both culturally and socioeconomically to the target communities in this study, to test device acceptability and protocol adherence.

Evaluation of the community arts projects in both the intervention and comparison communities relies on a qualitative methodology. To assess the impact of the community art projects, focus groups are conducted. Kieffer et. al (2005) suggest that focus groups be used to help researchers build a deeper understanding of the community and the impact of the intervention on the community [33]. In attempts to quantify these impacts and change in the level of civic engagement, the focus group data will be used to develop a community engagement survey that will be implemented in year 2, 3, and 4 of the intervention. The instrument will be piloted in a rural community that will serve as comparison for the validation of the instrument prior to implementation.

